### Trial design

The study will be a randomised, controlled, evaluator-blinded prospective parallel-group trial based on the Consolidated Standards of Reporting Trials (CONSORT) statement regarding the randomised trial of non-pharmacological treatments [40]. There will be two arms, baby-CIMT and baby-massage; children randomised to either arm will receive two 6-week training periods separated by a 6-week break (Figure 1). The study setting is Astrid Lindgren Children’s Hospital, a tertiary hospital in Stockholm, Sweden.

**Figure 1 F1:**
[figure not shown]
Flowchart of a baby-CIMT trial according to CONSORT guidelines.

#### Recruitment of children at risk of developing unilateral CP

Two groups of children will be invited: 1) infants at risk of developing unilateral CP due to a known neonatal event affecting the brain and 2) infants referred to Astrid Lindgren Children’s Hospital due to asymmetric hand function. A known etiological cause of the asymmetric hand use is not a prerequisite for referral, i.e., infants with neurological signs but without a diagnosis can be referred to the project. Recruitment (different from inclusion) is based on broad inclusion criteria in order not to overlook children who may later develop unilateral CP; the diagnosis will be followed up at a higher age. Signs of asymmetric hand use will be confirmed using the Hand Assessment for Infants (HAI). If clinical signs of asymmetry are inconclusive at referral, a second investigation will be performed one month later. Neuropediatricians and neonatologists in Stockholm-area hospitals will be informed of the study through seminars and hand-outs.

#### Participants

Infants are eligible to enter the study based on the following inclusion criteria: 1) 3–8 months of age, corrected age (CA) being used for preterm infants, and 2) clinical signs of asymmetric hand use, confirmed by the asymmetry score on the primary outcome measure HAI. Exclusion criteria will be severe visual impairment, seizures not controlled by antiepileptic drugs, and children with clinical signs of bilateral involvement.

Inclusion at 3–4 months of age is based on typical infant development of self-initiated actions. Before this age, self-initiated actions are difficult to measure and hand asymmetries difficult to detect using HAI. Information from HAI video-recordings indicates that, at this age, infants begin to be interested in the test toys; at 3–4 months, the children’s grasping ability is still limited but their interest in handling toys is increasing, making it possible to initiate baby-CIMT. Children will be included no later than at 8 months of age because the protocol lasts 18 weeks and the intervention is intended to finish before the children are 1 year old.

At 1 year of age, or 1 year CA, the children will be examined by a paediatric neurologist. Children who meet the Surveillance for Cerebral Palsy in Europe (SCPE) criteria at this time will be diagnosed as likely having unilateral CP. The diagnosis will be based on a neurological examination and thorough history, including aspects of fine and gross motor development and information regarding neonatal events. Preterm birth, neonatal stroke, asphyxia, or other incidents such as meningitis or insults after early heart surgery will be considered. If known, we will also consider brain imaging results indicating conditions such as predominantly unilateral haemorrhage or early signs of white matter damage of immaturity (WMDI), neonatal stroke, and malformations. The CP diagnosis and subtype will be updated as other symptoms may appear later.

#### Randomisation

Eligible infants will be randomly assigned to the baby-massage or baby-CIMT groups in a block design. The infants will be stratified by age and neonatal events, with three age groups, i.e., 3–4, 5–6, and 7–8 months, and three neonatal event groups, i.e., neonatal stroke in full-term infants (> week 37), preterm birth (< week 37), and unknown/other. This stratification is chosen to ensure that the study groups will be approximately equally distributed based on age and neonatal events.

Infants will be recruited consecutively. Randomisation will occur after the first assessment, ensuring that the assessing occupational therapist will not be biased at this time by knowing the group assignment. A random number list that also contains stratification alternatives will be generated before the start of the study and kept by the Principal Investigator (PI) in a locked room. When an infant is recruited, relevant stratification information will be given to the PI; the infant will then be assigned to the next position and added to the list by the PI. If an infant is later excluded for any reason, the infant’s position in the randomisation list will not be replaced by any new infants.

#### Blinding

Families will not be blinded to group allocation, though they will be blinded to the study hypotheses. The occupational therapist responsible for data collection (i.e., administration and filming of HAI and AHA) will not be blinded to group allocation. However, the occupational therapist scoring the video recordings of HAI and AHA will be blinded to group allocation. The physiotherapist administering the Alberta Infant Motor Scale will not be otherwise involved in the study (see “Outcome measure and procedure”).

### Sample size

The estimated number of participants needed to achieve the study objectives is based on HAI data obtained from a pilot group of 12-month-old infants who received either studied intervention. Based on a two-tailed test of two independent means, with a significance (α) level of 0.05 and 80% power, we require 16 participants in each group for a total sample of 32.

#### Baby-CIMT

This programme will be based on experience from a pilot group of infants, previous work with children older than 18 months, and the theoretical considerations described in the introduction. The reasons for choosing the training dosage and type of restraint will be reported and various programme components further described.

##### Restraint type and training dosage

Any kind of simple restraint can be used on the non-involved hand. The restraint is only used during the training. From the pilot group we learned that young infants will rarely remove the restraint but will commonly start to use the involved hand as soon as the non-involved hand is rendered less useful by the imposition of a soft restraint. We prefer to keep the restraint simple and comfortable, so a sock or mitt can be used as well as a bag clip at the end of a long-sleeved sweater.

The total dosage will be 36 hours, administered over the two 6-week training periods. The most effective combination of training hours/day and length of training period is currently unknown even for older children [25]. In the present study, we have chosen 30 minutes per day of training based on practical considerations and feasibility. First, the attention span of infants is short: even 30 minutes can be too long and may sometimes need to be divided into two shorter sessions. Second, limited time is available when young infants are alert and awake and this time needs to be shared with other caring needs. To obtain a reasonably high dosage, the length of the programme will be 12 weeks. Parents like to divide the time into two 6-week periods; it gives them time to focus on other things between the periods of treatment and it means that the overall treatment time frame is longer within the first year of life. This longer period takes advantage of the children’s developmental progression in relation to handling toys. Concern has been raised that restraining the non-involved hand may negatively affect its development. This concern will be addressed by means of the short duration of daily restraint and the infants’ continued use of both hands outside the treatment time. We also assume that the infants will immediately start to apply what they learned in the training session at other times of the day. By using HAI as an outcome measure, it will also be possible to monitor the development of each hand separately.

##### Components of baby-CIMT programme

Baby-CIMT includes several components in which training in grasping action and toy exploration is the main focus. However, the training will not be effective if it is not integrated with the other theoretical assumptions, including the expectations and attitudes towards the infant and families (see “Background”). The need for a rich environment, selection of toys at the right ability level, optimal child positioning, and the education and supervision of the parents as treatment providers are important components of the baby-CIMT intervention.

##### Attitudes towards the infant

Both therapists and parents must be aware of and recognise the infants’ response pattern and their intention to grasp and explore objects as well as interact and communicate. In general, young infants react slowly and, compared with older children, they take considerable time to initiate motor actions; infants with an affected hand are even slower to initiate actions. Some key advice is to: a) wait for the child’s intention while holding his or her attention; b) attract the child’s attention and encourage him/her to act, but without forcing; c) reinforce and respond positively to the child’s actions; and d) stop the training when the child becomes tired and stops cooperating.

##### Toy selection for training dependent on infant’s ability

Toy selection is vital for the ability to practise various hand actions. Importantly, toys can be any play objects of interest. When choosing a toy, the infant’s age, cognitive level, and motor ability must be taken into consideration. It is important to choose toys and expect motor actions to the appropriate ability level. Young infants or infants with limited motor ability need at first to learn to initiate reaching toward objects. Toys needs to be within their reaching distance to stimulate touching and moving the objects and certain pre-grasping behaviors. To stimulate grasping, easily grasped toys must be presented near the hand that is expected to grasp. When the manual ability of infants become more advanced, they will develop their grasping ability and become interested in exploring objects. At this ability level, infants like to have a lot of toys to explore and numerous grasping actions can easily be promoted. Infants typically explore and manipulate toys and other play objects by banging, fingering, mouthing, slapping, and dropping them. Thereafter, the infants have to refine the quality of grasping and object manipulation. This means that one must give infants a series of small objects to pick up to stimulate precise grasping, well-adapted to the objects’ properties. Importantly, the infants have to continue to practice on their ability level. The challenge for therapists is to choose toys and play situation on an appropriate ability level, not to difficult not to easy. Result on the HAI can guide the decisions.

Families are advised to collect toys and play objects for the training sessions in a special basket; these toys should be used only during the training sessions. It is known that new things are more attractive than familiar things and that even young infants are more likely to look at and manipulate novel toys than familiar toys [41]. There should be many toys in the basket in order to promote repetition. To elicit the different motor actions the toys also needs to have different characteristics. Play objects must be of appropriate size and weight according to the infant’s grasping ability. Likewise, the toys have to be made of various materials ensuring the infant interest in object exploration. Many objects in the environment are interesting to infants, including necklaces, kitchen utensils, Christmas decorations, soft packages, and natural items such as stones and pinecones. As the infants become older, they must be presented with new toys matching their cognitive level.

##### Position of infants and parents during hand training

The parents should always be positioned in front of the infant to facilitate interaction and allow the parents to easily see the infant’s reaction to the toys. In general, the infant should be sitting in as upright and stable position as possible to facilitate self-initiated actions [42]. Before they are able to sit, infants can be placed in a baby seat/bouncer; when the infants can sit in a high chair, this is preferable. If the infant is somewhat unstable, small pillows should be used to provide stability: we do not want the infant to have to concentrate on maintaining sitting balance when trying to use his or her hand. When an ordinary table is used, it should not be too high. When the infant is able to sit independently, he or she can of course be on the floor. The prone position should be avoided for hand training, we do not want them to practice weight bearing concurrently with object manipulation.

##### Therapist’s role and attitudes towards the family

It is known that parents can be effective treatment providers if they are properly trained and supervised [25,43]. To ensure high-quality training, participating families will receive supervision, coaching, and education during weekly home visits from an occupational therapist. The attitude of the therapist is crucial to training success, as the therapist must: a) support the parents’ sense of self-efficacy and confidence as treatment providers, so they can make the treatment situation enjoyable; b) empower the parents as problem solvers and experts regarding their child’s ability, as people who can use their creativity to find suitable toys for practice; c) ask questions that are open-ended and thus help parents come up with their own answers; and d) summarise what is discussed in the training sessions.

##### Information material and parent education

Parents will be given a folder of material presenting the various aspects of the programme from a family perspective. It includes a diary for recording training times/durations, notes for focus areas, and mind maps of important questions to consider before and after the daily training. The folder will also include suggestion of play material and written information addressing particular concerns and interests. Questions to be covered in the weekly home visits include: What is baby-CIMT? What is known about the effects of the method? Why is early training important? What is known about the development of hand function in children with unilateral CP?

#### Baby-massage

At the start of the first treatment period, parents in the baby-massage group will receive a three-session individualised instructional course from a certified baby-massage instructor. The sessions will be held once weekly for the first 3 weeks of the period. During the course, the parents will receive verbal and hands-on training about the purpose and mode of the massage, practising the technique on their infants under instructor supervision. The programme will cover full-body massage using a small amount of massage oil. Parents will be taught to massage each body part in sequence using slow and gentle strokes, smooth circular movements, and gentle squeezing depending on the body part. An instruction sheet will be given to parents, who will practice the technique on an ongoing basis at home.

For the daily practice, parents are instructed to choose a time of day when the infant is calm and the parents feel relaxed. A full programme takes about 30 minutes, but a partial session can be administered depending on the infant’s mood. Baby-massage is only successful if both parents and infant are enjoying the situation and must be stopped if the infant displays any distress at the practice. The massage times/durations will be noted in a diary.

### Outcome measure and procedure

The study timeline is presented in Figure 1. The outcome measure will be determined at the start of the intervention, 12 months after the intervention, and at 2 years of age. The infants will be monitored using the Hand Assessment for Infants (HAI) tool, the Alberta Infant Motor Scale (AIMS), and the Parenting Sense of Competence Scale (PSCS). Additional HAI data will be collected after the first treatment period of 6 weeks of training, after the 6 weeks of no training, after the second treatment period of 6 weeks of training and at 12 months. AHA will be administered at 2 years of age.

#### Primary outcome measure is the Hand Assessment for Infants, HAI

HAI, which is currently being developed by [name] et al. [24,44], is intended to evaluate the quality of goal-directed manual actions in infants, 3–12 months of age, at risk of developing unilateral CP. The test procedure comprises a semi-structured video-recorded 10–15-min play session. The child is seated in a baby seat/bouncer or a high chair depending on his or her age. The chair should not restrict arm movements and as upright a position as possible should be striven for. A test kit of carefully selected toys will be presented to the infant to encourage and elicit exploration, making a wide range of motor actions observable. The set-up and administration of the play session are crucial for the possibility of observing and scoring the infant’s manual abilities. Scoring is performed from the video-recording. HAI is intended to detect and quantify possible asymmetry between hands by providing scores for each hand separately, and to provide a measure of bilateral hand use. Both criterion- and norm-referenced outcome measures will be provided. HAI is still under development, but the preliminary scale consists of 18 items (13 unimanual and 5 bimanual) each scored using a 3-point rating scale. Preliminary Rasch analysis indicates promising results in terms of internal construct validity and unidimensionality.

#### Secondary assessment

##### Questionnaire about parent’s experience of treatment

The parents will be asked about their experience of the interventions. These questions will address the feasibility of the intervention programme and the family’s impression of its effects; the responses will be recorded using a 4-point scale.

##### Parenting sense of competence scale, PSOC

The PSOC scale measures parents’ sense of confidence and satisfaction using a self-reported questionnaire [45,46]. Both mothers and fathers will be asked to complete the questionnaire. PSOC contains 16 statements to which the parents can respond in a six level Likert type scale, ranging from agreement to disagreement. The questionnaire yields two subscales: *skills* captures parental self-perceptions of skill and knowledge regarding parental functions, while *valuing* captures feelings of satisfaction, frustration, and interest associated with parenting. Satisfactory psychometric properties were reported by the original authors [46] and more recently by Gilmore and Cuskelly [47].

##### Alberta Infant Motor Scale, AIMS

AIMS identifies delayed or deviant motor development. It assesses the gross motor performance of infants relative to a norm-referenced sample aged 0–18 months [48,49]. It is an observational assessment focusing on milestones and the quality of posture and movement. It includes 58 items regarding prone, supine, sitting, and standing positions and the results are reported as a composite score. AIMS has good psychometric properties [48,49] and has been specially investigated for application to preterm babies [50].

##### Neuroimaging

Brain lesion characteristics will be investigated using neuroimaging scans acquired for clinical purposes. The age at imaging can vary, but we would mainly use scans performed after the age of 6 months. Conventional structural Magnetic resonance imaging (MRI) will be acquired using various imaging protocols and equipment. A 3.0 T MRI system will be used in the Astrid Lindgren Children’s Hospital. All images will be visually reassessed specifically for this study by experienced neuroradiologists unaware of the infants’ clinical diagnosis and functional outcome. The analytical protocol was developed in our group and has been applied in previous studies [51] using the primary patterns of abnormality defined and described by Ashwal et al. [52]. The basic patterns of damage will be classified as normal, white-matter damage of immaturity (WMDI), focal ischaemic or haemorrhagic lesions, brain malformations, diffuse encephalopathy infection, and miscellaneous or unclassifiable lesions.

##### Assisting Hand Assessment, AHA

The AHA, for children aged 18 months to 12 years, examines how effectively the children use their affected hand in bimanual activities [53]. A 15-minute play session is video recorded, and then 22 items are scored on a 4-point rating scale (AHA version 4.4). The total raw score is converted to an interval scale of AHA units ranging from 0 to 100 [54] where a higher measure indicates higher ability.

### Statistical methods

Analyses will be conducted on an intention-to-treat basis. Data for each assessment will be summarised for each treatment group and the descriptive statistics will be calculated depending on the data distribution for each assessment. HAI outcomes will collected at the times defined in the study protocol. The *primary efficacy variable* will be the mean change in the HAI score from baseline to the last post-treatment period after 18 weeks. The *secondary efficacy variable* will be the mean change in the HAI score from baseline to the first post-treatment period after 6 weeks and from baseline to the age of 1 year. The mean change in HAI score will be analysed using ANCOVA, including the baseline as covariate and group as a fixed factor in the model. Another efficacy variable will be the proportions of infants with improved HAI scores from baseline to the first post-treatment period after 6 weeks, to the end of the second treatment period after 18 weeks, and to the age of 1 year. The proportions will be analysed using logistic regression including baseline as covariate and group as a fixed factor. An odds ratio of > 1 will be interpreted as indicating an increased chance of improved HAI score. A significance level of 0.05 will be used.

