### Primary objective

The primary objective of the study is to investigate the effects of baby-CIMT and baby-massage on the development of manual ability in the first year of life of infants at risk of developing unilateral CP.

The specific hypotheses to be tested are:

1. Baby-CIMT is a feasible method for families and infants below one year of age.

2. Infants receiving baby-CIMT will develop manual ability in the involved hand faster than will infants receiving baby-massage in the first year of life.

3. Improvement of manual ability in the involved hand will be faster during the training period than during a period without training in the baby-CIMT group.

4. The manual development of the involved hand will depend on the type of brain lesion. Infants born at term with neonatal stroke are expected to develop more slowly than will preterm infants with mainly white matter lesions, independent of group allocation.

5. Development of manual ability in the non-involved hands will not differ between groups.

6. The assumed difference in manual development in the involved hand at 1 year of age depends on group allocation and the difference will remain at 2 years of age.

The secondary objective is to investigate whether the different treatment protocols influence the parents’ self-rated parenting competence.

1. Parents in the baby-CIMT programme will feel more competent at parenting than will parents in the baby-massage group since they will have learned more about the child’s specific needs.

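### The ANCOVA for change in HAI omits age and neonatal event, on which randomisation is stratified; if these predict change beyond baseline HAI, precision is lost and the test is conservative

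*Protocol article*

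**What the plan says.** Under Statistical methods, the primary efficacy variable "will be the mean change in the HAI score from baseline to the last post-treatment period after 18 weeks". This and the changes to 6 weeks and to 1 year of age are to be "analysed using ANCOVA, including the baseline as covariate and group as a fixed factor in the model". No other term is named there. The Abstract mentions only generalised linear models and lists no covariates.

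Under Randomisation, infants are "assigned to the baby-massage or baby-CIMT groups in a block design". "The infants will be stratified by age and neonatal events, with three age groups" (3–4, 5–6 and 7–8 months) and three event groups: "neonatal stroke in full-term infants (> week 37), preterm birth (< week 37), and unknown/other". That makes nine strata. The block size is not given.

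Under Primary objective, hypothesis 4 states: "The manual development of the involved hand will depend on the type of brain lesion". It adds: "Infants born at term with neonatal stroke are expected to develop more slowly than will preterm infants with mainly white matter lesions", whichever group they are in.

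For age the expectation is only implied. At 3–4 months, Participants says, "grasping ability is still limited but their interest in handling toys is increasing", and the Background hypothesises that treatment at an early age will affect later development.

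**The concern.** Blocking within strata removes part of the between-stratum variation from the treatment comparison. A model without the strata still counts that variation as residual error. Its standard error then describes a less precise design than the one that was run: the test rejects less often than 5% under the null, and the interval is wider than it needs to be. In a trial of 32 infants this gives up precision that stratification could have provided. Any chance imbalance in age or event left by incomplete blocks also goes uncorrected, and it is likely, since 32/9 is about 3.6 infants per stratum.

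Age deserves particular thought for the change to 1 year. An infant entering at 3 months has about 12 − 3 = 9 months in which to change; one entering at 8 months has about 12 − 8 = 4. At the 18-week visit (about 4.1 months after entry) infants are roughly 7 to 12 months old.

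The model terms are written out in the protocol, so the point concerns what it fixes, not something left to an analysis plan that is not shown.

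**Working it through.** **Inputs from the protocol.** Two-sided α 0.05, 80% power, 16 per group (Sample size); model terms (Statistical methods); 3 × 3 = 9 strata (Randomisation).

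**Assumptions, not in the protocol.** Block size 2 or 4. R², the share of the variance in HAI change left after baseline that age and event explain, split equally between the two. Standardised difference d, measured against the SD left after baseline.

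**The plan's own figure.** No effect size or SD is stated, so 16 per group cannot be derived forward. Solving backward with the noncentral t-test, 16 per group is the required size for d between 1.02 and 1.06. I use 1.02. As a check on the planned model, residual df = 32 − 3 = 29 and SE = √(1/16 + 1/16) = 0.354 SD, which gives power 0.799.

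**Analytic bound.** Adding continuous age (1 df) and event (2 df) leaves 32 − 6 = 26 df and multiplies the SE by √(1 − R²). At R² = 0.30 the multiplier is √0.70 = 0.837 and power is 0.915; at 0.10 it is 0.949 and 0.836; at 0 it is 1 and 0.796. This overstates the gain, because it gives the planned analysis no credit for stratification and assumes perfect balance on the added terms.

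**Simulation.** 32 infants, nine strata, permuted blocks, 4,000 trials per cell, so each power has a Monte Carlo error of about √(0.8 × 0.2/4000) = 0.6 points. The adjusted model adds continuous age and three-level event. Paired entries are blocks of 2 / blocks of 4.

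| R² | Type I error, planned (%) | Power, planned (%) | Power, adjusted (%) | Change (points) |
|---|---|---|---|---|
| 0 | 4.7 / 4.8 | 78.4 / 77.6 | 77.3 / 76.1 | −1.1 / −1.5 |
| 0.10 | 4.4 / 3.5 | 80.2 / 79.6 | 82.0 / 81.1 | +1.8 / +1.5 |
| 0.20 | 3.4 / 3.6 | 80.0 / 79.0 | 85.7 / 84.4 | +5.7 / +5.4 |
| 0.30 | 2.8 / 2.8 | 81.8 / 81.4 | 90.6 / 89.3 | +8.8 / +7.9 |
| 0.50 | 1.0 / 1.5 | 84.8 / 82.7 | 97.2 / 96.7 | +12.4 / +14.0 |

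The adjusted test's type I error lies between 4.4% and 5.2% throughout. A second simulation of the same design gave 79% planned against 82–83% adjusted at R² = 0.15 (+3 to +4), and 81–83% against 95% at 0.45 (+12 to +14). Across all runs at 0.30, planned power was 78–82% and adjusted power 88–90%.

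**Where the gain comes from, at R² = 0.30.** The planned model reports a mean SE of 0.36, while its estimate actually varies with an SD of about 0.315: 0.36/0.315 = 1.14, so the SE is overstated by about 14%. The adjusted SE is about 0.305: 0.305/0.36 = 0.85, so intervals are about 15% narrower.

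**Break-even.** Adjustment starts to pay at R² of about 0.02 analytically and roughly 0.05 by simulation.

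**The case against.** The strongest reply is that the planned analysis does what the protocol promises. The estimate is unbiased, the test errs on the safe side, and simulated power stays near 80% (about 78–85% across the scenarios). The shortfall is against a better model, not against the sample size statement. That stands. A reader might infer that the trial is underpowered or its analysis invalid; the documents do not support either.

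The loss also depends on an R² that the protocol does not give. Hypothesis 4 is explicit for lesion type, but nothing says age predicts change once baseline HAI is in the model, and baseline HAI will carry part of any age effect. Stratification is justified only as a way to balance the groups. That stands too, and is why the result is given as a range starting at zero.

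Block size matters. With blocks of 8 at R² = 0.30, the planned type I error is about 3.1–3.7%, closer to nominal, because less of the stratum variation is balanced out. The power gap remains about 8–9 points. With blocks of 8 and R² = 0, adjustment can cost up to 3.5 points.

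Two further inferences are tempting and should not be drawn. The logistic model for the proportion improved has the same two terms, but residual-variance reasoning does not carry over: adjustment changes the odds ratio being estimated and generally increases its standard error, and extra terms with 32 infants risk separation if nearly all improve. Nor would the event term test hypothesis 4 itself. That hypothesis concerns lesion type, which the Neuroimaging section classifies from reassessed scans; a preterm infant need not have a white-matter lesion, and the unknown/other group mixes lesion types. The stratum is only a proxy.

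**Conclusion.** The point holds as an efficiency and calibration issue in the ANCOVA. The omission is certain; its size is conditional. If age and event explain little beyond baseline HAI, nothing is lost and adjusting costs 1–2 points of power. If they explain about 30% of the remaining variance, the planned test runs at about 2–3% type I error and gives up 8–10 points of power; at 45% it gives up about 12–14. These figures rest on blocks of 2 or 4, d of about 1.02 back-solved from the sample size, and equal contributions from the two factors. The trade favours adjusting, because the downside is small and the break-even share low. The change is worth making, but the planned analysis is not invalid without it.

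**What to change.** Change the model sentence under Statistical methods so that the ANCOVA for change in HAI at 6 weeks, 18 weeks and 1 year contains group, baseline HAI, baseline age (corrected for preterm infants, continuous) and neonatal event group (three levels), as main effects only. Do not fit the nine strata as separate cells: that takes 8 df instead of 3 for no gain in power (0.910 against 0.915 analytically at R² = 0.30).

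The cost is one sentence, no new data, 3 residual df (29 to 26), and 1–2 points of power if the factors are not prognostic with small blocks. Leave the logistic model outside this change, and do not present the event coefficient as the test of hypothesis 4.
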